## Abstract

**Background:**

Autism Spectrum Disorder (ASD) is a neurodevelopmental disorder characterised by persistent deficits in social communication and the presence of restricted, repetitive behaviours or interests. Previous literature has identified a link between the gut and ASD; however, the underlying mechanisms remain unclear. Gut microbiota dysbiosis has been extensively reported in cohort studies of ASD, and specific microbial metabolites or by-products may serve as potential biomarkers for ASD. Additionally, children with ASD often exhibit food refusal, have a limited food repertoire and display a tendency to consume the same foods frequently; thus, these behaviours increase their risk of malnutrition (over-nutrition or under-nutrition) compared to typically developing (TD) healthy children. This study primarily aims to identify oral and gut microbiota among children with ASD and TD healthy children. The secondary aim is to determine the associations between oral and gut microbiota with nutritional status among children with ASD. The findings will enhance understanding of the aetiology of ASD and inform early intervention strategies to mitigate disease severity and early identification of malnutrition in genetically at-risk children.

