**Methods and analysis:**

This observational, age-matched, case-control study is conducted in Malaysia among 40 male children with ASD and age-matched with 40 TD healthy controls aged 4–10 years. The dependent variables include the microbiota profile, identified through metagenomic sequencing analysis of saliva and faecal samples, and autism severity, assessed through validated questionnaires. Independent variables include nutritional status, determined through Subjective Global Nutrition Assessment (SGNA), anthropometry and dietary measurements, gastrointestinal symptoms, eating behaviour, behavioural profile, and sleep quality. Data collection is expected to be completed by June 2026. The study nature may limit causality establishment. Analyses will use chi-square/ANOVA for group comparisons, SparCC for microbiota correlations, and mixed-effects logistic regression to model associations.

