Children with ASD are frequently associated with disruptive mealtime behaviours, such as severe food refusal, a limited food repertoire, and high-frequency single-food intake [8]. These behaviours are closely related to sensory processing difficulties, such as aversion to specific textures, smells, and tastes [9]. Consequently, children with ASD are at an elevated risk of poor nutritional status. A local study conducted among 224 children with ASD in Kuala Lumpur reported that the prevalence of underweight, stunting, wasting/thinness and overweight/obesity were 9.3%, 8.0%, 4.0%, and 21.5%, respectively [10]. Another recent study in central region of Malaysia (Selangor, Kuala Lumpur, and Negeri Sembilan) involving a total sample size of 150 children with ASD documented that 15% of the children were underweight, and 52% were overweight and obese [11]. Although most children had adequate total energy and protein intakes, their fat intake exceeded the recommended levels [10]. Moreover, the majority of the children did not meet the Recommended Nutrient Intake (RNI) requirements for several key nutrients, including fibre (99.6%), thiamine (67.4%), vitamin C (50.9%), vitamin D (98.2%), vitamin E (74.6%), vitamin B12 (64.3%), folate (88.8%), calcium (90.2%), and zinc (77.2%) [10]. Therefore, a comprehensive understanding of the nutritional risks faced by children with ASD is essential for healthcare professionals to develop effective, targeted nutritional interventions.

Research has shown that children with ASD may exhibit altered nutrient metabolism, including deficiencies in essentials vitamins and minerals, which could contribute to the development and progression of the disorder. For example, studies have reported lower levels of vitamins B6 and B12 in children with ASD, both of are critical for neurological function [12–14]. Dietary habits are considered one of the main factors influencing the diversity of human gut microbiota [15]. Furthermore, host genetics, dietary habits, gut physiology, hygiene level, stress, and physical activity influence the gut microbiota. The human gut “metagenome” is a complex consortium of trillions of microbes, whose collective genomes contain over 100 times as many genes as the human eukaryote genome [16]. This essential “organ,” the microbiome, provides the host with protection against pathogens, enhancement of immune system and metabolic capabilities, as well as modulation of gastrointestinal (GI) development [17].

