### Nutritional status and dietary assessment

A Subjective Global Nutrition Assessment (SGNA) will be utilised to determine the nutritional status of the children [49]. SGNA evaluates nutritional status in two main categories: Nutrition Focused Medical History (NFMH) and Physical Exam (PE). NFMH includes evaluating the appropriateness of current height and weight for age, changes in body weight, dietary adequacy, gastrointestinal symptoms, functional capacity, and metabolic aspects of disease. PE evaluates subcutaneous fat loss, muscle wasting, and nutrition-related oedema. The combined NFMH and PE evaluation will generate an overall SGNA ranking of normal/well-nourished, moderately malnourished, severely malnourished [49].

Dietary intake of the children will be obtained through parental interviews, using 3-day dietary recalls (two weekdays and one weekend day). To assist with the food intake portion size estimation, pictures of household measuring tools will be provided. Detailed information about the food and beverages consumed, such as cooking methods and brand names (if applicable), will be recorded. Nutrient analysis will be generated using the Nutritionist Pro^TM^ Diet Analysis software (Axxya Systems LLC, USA) and the Malaysian Food Composition Database (MyFCD). Nutrient adequacy will be assessed by comparing the intake to the Malaysian Recommended Nutrient Intakes (RNIs) [50]. Adequate intake will be defined as meeting or exceeding 100% of the RNI for macro- and micronutrients Portion size estimation in dietary assessment has been validated as reliable [51]. As dietary data will be parent-reported, research assistant will verify accuracy by reconfirming food intake during data entry prior to nutrient analysis. Basal metabolic rate (BMR) will also be calculated to identify potential underreporting or overreporting of energy intake.

Anthropometric measurements will be conducted by trained research assistant ([name]), a registered dietitian who completed standardized anthropometric assessment training measurement according to the standardized guideline by ISAK [52]. Observer and assessor training will be provided to research staff while obtaining data on 3-days dietary recall, with peer review and error checks to ensure data reliability.

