### Statistical analysis plan

Data analysis will be conducted using R software and its available packages. The differences in microbiota profiles, socio-demographic factors, emotional and eating behaviour, and nutritional status between children with ASD and TD children will be compared using the chi-square/Fisher’s exact test and ANOVA where appropriate. Student’s t-test will be applied to compare BMI and age between groups. Pre-filtering and inference of correlations will be performed using the Sparse Correlations for Compositional Data (SparCC) correlation metric [66], with a minimum R-value threshold of 0.35. SparCC will be used to correlate salivary and faecal bacterial markers detected in saliva and faecal samples from the same child. The associations between microbiota profiles, socio-demographic factors, emotional and eating behaviour, autism severity, sleep quality, gastrointestinal symptoms, and nutritional status among children with ASD will be modelled using mixed-effects logistic regression (MELR) model and random forest. Normality, linearity, homoscedasticity, and multi-collinearity will be assessed to ensure that the assumptions of regression models are met. Potential confounders, including age, and socioeconomic status will be adjusted for fixed effects. Model assumptions will be performed using DHARMa package in R to assess dispersion, zero-inflation and overall fit [67]. In case of heteroscedasticity or overdispersion, corrective strategies will include the use of an observation-level random effect, modelling dispersion or zero-inflation with glmmTMB [68], or applying bias-reduced logistic regression (Firth correction) [69] or bootstrap inference to mitigate small-sample bias [70]. Study results are expected in December 2026.

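### Nutritional status is a primary outcome, but the Methods assign it to SGNA, which shows no grade for over-nutrition, and BMI-for-age z is calculated but never named for analysis

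*Protocol article*

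**What the plan says.** The Sample size section names two primary outcomes, microbial beta diversity and nutritional status. The Abstract (Background) describes a "risk of malnutrition (over-nutrition or under-nutrition", so both directions count.

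The protocol describes how nutritional status is obtained in several places:

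- Abstract (Methods and analysis), in its list of independent variables: "nutritional status, determined through Subjective Global Nutrition Assessment (SGNA), anthropometry and dietary measurements".
- Nutritional status and dietary assessment: "A Subjective Global Nutrition Assessment (SGNA) will be utilised to determine the nutritional status of the children". The result is "an overall SGNA ranking of normal/well-nourished, moderately malnourished, severely malnourished". The physical examination covers loss of subcutaneous fat, muscle wasting and oedema.
- Anthropometric data: BAZ, height-for-age z (HAZ) and weight-for-age z (WAZ) are calculated and classified against the WHO standards and reference.
- Statistical analysis plan: a "t-test will be applied to compare BMI and age between groups". Nutritional status appears there as a separate item with no measure attached, and BAZ is not mentioned.

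The intake rule, also under Nutritional status and dietary assessment, reads: "Adequate intake will be defined as meeting or exceeding 100% of the RNI for macro- and micronutrients".

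The Background cites two local studies of children with ASD. One (224 children) found 9.3% underweight and 21.5% overweight or obese. In the other (150 children), "15% of the children were underweight, and 52% were overweight and obese". The first study also reported that "their fat intake exceeded the recommended levels".

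**The concern.** In both cited local studies overweight is the commoner problem, by 21.5/9.3 = 2.3 times in one and 52/15 = 3.5 times in the other. Yet the Methods sentence on nutritional status points to the one instrument whose grades run only from well-nourished to severely malnourished. BAZ, which can register both tails, is calculated but given no role in the analysis section.

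Three things are at stake. First, one obese child could be well-nourished by SGNA and obese by BAZ on the same primary outcome, with no rule to say which counts, so the choice could be made after the data are seen. Second, if SGNA is the variable used, overweight children sit in the reference group and weaken any contrast related to over-nutrition. Third, the intake rule cannot separate sufficient from excessive macronutrient intake, although excess fat is one of the findings the protocol cites as background.

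**Working it through.** The protocol gives no figure of its own for this point, so there is none to reproduce. The inputs are the prevalences in the Background and the planned 40 ASD children (Sample size section).

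**Expected counts among 40 ASD children** (40 × prevalence)

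| Status | First study | Second study |
|---|---|---|
| Overweight or obese | 40 × 0.215 = 8.6 | 40 × 0.52 = 20.8 |
| Underweight | 40 × 0.093 = 3.7 | 40 × 0.15 = 6.0 |

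**Make-up of the SGNA well-nourished group.** Assume that SGNA flags exactly the underweight children. The overweight share of those left is p(over) / (1 − p(under)):

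- First study: 0.215 / 0.907 = 0.237, about 24%.
- Second study: 0.52 / 0.85 = 0.612, about 61%.

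If SGNA flagged no child at all, the shares would be the raw prevalences, 21.5% and 52%, so the result does not depend much on how sensitive SGNA is to underweight.

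**Can SGNA register excess by another route?** Its history part asks whether height and weight are appropriate for age and gives no direction. An assessor might mark an obese child down there. The only grades below well-nourished are moderate and severe malnutrition, so that child would share a grade with under-nourished children. On the protocol's description, the ranking carries no direction either way.

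**Raw BMI.** Ages run from 4 to 10 years. Controls are matched within 6 months (Study population and setting) and all children are male (Sample size section). The two groups should therefore have closely similar age distributions, and age should not materially bias the difference in mean BMI. What remains is age-related spread within each group, which costs precision, and a mean that cannot be read as under- or over-nutrition. The documents give no figure from which to size the precision loss.

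**Intake flag.** The first local study gives the percentage of children not meeting the RNI. The expected number meeting it is 40 × (1 − that proportion):

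- Fibre, 99.6% not meeting: 40 × 0.004 = 0.16.
- Vitamin D, 98.2%: 40 × 0.018 = 0.72.
- Calcium, 90.2%: 40 × 0.098 = 3.9.
- Folate, 88.8%: 40 × 0.112 = 4.5.

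Taking children as independent, the chance that none of 40 meets the RNI is 0.996^40 = 0.85 for fibre and 0.982^40 = 0.48 for vitamin D. For fat the problem is the opposite one: an intake above the recommended level satisfies the rule and is labelled adequate.

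**The case against.** A reader might infer that the plan cannot register over-nutrition and codes obesity as normal. The text does not support that. The Abstract makes anthropometry part of nutritional status, the Anthropometric data section commits to WHO classification of BAZ, and the Review of previous literature singles out BMI within nutritional status. An overweight child will be identified as such in the dataset. It follows that the count of about 9 to 21 overweight children hidden among the well-nourished, and the 24% to 61% share, apply only if SGNA alone is the analysed variable, which no passage states.

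It is also fair to say that SGNA's restriction to under-nutrition is inferred from its grade labels and examination items, since its scoring rules are not reproduced. The RNI rule defines adequacy of intake, not nutritional status, and the Statistical analysis plan section does not say that adequacy flags enter any model. The near-constant flags are thus a weakness of the stated coding, not a demonstrated failure of a planned model. The RNI figures come from ASD children only and say nothing about the controls. Matching and the single-sex sample largely answer any charge that raw BMI is confounded by age. Finally, a linear BAZ term would put under- and over-nutrition at opposite ends, so effects common to both could cancel.

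All of that stands. It does not settle which measure is the primary outcome, on which the Abstract and the Methods differ. It does not give BAZ a place in the analysis, nor put an upper bound on the macronutrient rule. These are definitions that the article states, not details it has left to a fuller document.

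**Conclusion.** The point holds in a limited form. Over-nutrition is measured, but the primary outcome is assigned in the Methods to an instrument with no evident category for it, elsewhere to three measures together, and the analysis section uses raw BMI in place of the age-standardised score. The possible consequence is sizeable: about 24% to 61% of the well-nourished group would be overweight or obese. It rests on three assumptions: SGNA alone is analysed, it flags exactly the underweight children, and the cited local prevalences carry over to this sample. Under those conditions an association between over-nutrition and microbiota would be diluted. The raw-BMI comparison is mainly a matter of precision and interpretability. The intake rule is a separate, smaller weakness: one-sided for macronutrients and nearly uninformative as a yes/no flag for fibre and vitamin D. The definitions should be settled before analysis begins.

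**What to change.** Reconcile the Abstract, Anthropometric data, Nutritional status and dietary assessment, and Statistical analysis plan sections as follows:

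1. Name WHO BAZ as the weight-status component of the primary nutritional-status outcome. Use continuous BAZ for the comparison of ASD and control children, in place of raw BMI.
2. In the association models, enter BAZ as WHO categories or with a non-linear term, so that under- and over-nutrition do not cancel.
3. Describe SGNA as the under-nutrition measure, and keep HAZ and WAZ as planned.
4. Analyse nutrient intake as continuous percentage of RNI. Report energy and macronutrients as below, within or above the recommended range, with the reference for the upper bound stated in advance.

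No new measurement is needed, since BAZ and nutrient intakes are already being derived. The cost is rewording, some recoding and a little extra analysis. With 40 ASD children, some BAZ categories will be small (about 4 to 6 underweight on the cited figures), which favours the non-linear continuous term where categories are sparse.

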### Parent report questionnaires

To analyse children’s eating behaviour, the Child’s Eating Behaviour Questionnaire (CEBQ), a standardized parent report questionnaire, will be used [53]. The CEBQ consists of 35 items, which are divided into eight subscales, which include food responsiveness (7 items), enjoyment of food (3 items), emotional overeating (3 items), desire to drink (3 items), satiety responsiveness (5 items), slowness in eating (4 items), emotional under-eating (4 items), and fussiness (6 items). Parents will rate the frequency of these behaviours using a 5-point scale: 1 representing never; 2 rarely; 3 sometimes; 4 often; and 5 always. The CEBQ subscale scores will be calculated by determining the mean score for each dimension, derived from the sum of the items divided by the number of items answered in each dimension. Higher scores reflect a higher intensity of the specific eating behaviour. For the five items with opposite phrasing, scores will be reversed according to the instrument’s instructions. CEBQ demonstrates good internal consistency, with Cronbach’s alpha ranging between 0.72 to 0.91, and adequate test-retest reliability (r = 0.52–0.87) [54]. The factorial validity of CEBQ has been evaluated in a study conducted on Dutch children, with Cronbach’s alpha ranging from 0.75 to 0.91, replicating the original eight-factor structure of the questionnaire and supporting its applicability across cultures [54]. Moreover, CEBQ has been validated among Malaysian children, showing good internal consistency within the subscales and widespread use in similar research [55].

Gastrointestinal (GI) symptoms will be assessed using a modified version of the GI Severity Index (6-GSI), which encompasses six items: constipation, diarrhoea, stool consistency, stool smell, flatulence, and abdominal pain [56]. Parents will rate their child’s GI symptoms on a three-point Likert scale, with scores of 0, 1 or 2 based on the severity and frequency of the symptoms experienced over the past three months. A score of 0 indicates the absence of symptoms, while scores of 1 and 2 reflect varying severity levels of the present symptom. A total score of 3 or higher will be considered a high score, while a score of below 3 will be considered as a low score [56]. The total GI score has a high intraclass correlation of 0.95 [95% CI: 0.87–0.98]. [57]

Furthermore, the Autism Treatment Evaluation Checklist (ATEC) is an instrument designed to quantitatively assess the effectiveness of treatments for children with ASD [58]. ATEC composes 77 items distributed across four subscales: 1) speech/language/communication, 2) sociability, 3) sensory/cognitive awareness, and 4) health/physical behaviour. The sum of the scores for each subscale gives the total ATEC score ranging from 0 to 179. For the interest of this study, only the first subscale, speech/language/communication (14 items) will be utilized to assess the language ability of children with ASD, with scores for this section ranging from 0 to 28. A lower total score indicates less severe symptoms of ASD, while a higher total score correlates with more severe symptoms of ASD. The internal reliability of ATEC is very high, with a total score reliability of 0.94, based on a split-half reliability test conducted on over 1,300 completed ATECs [59]. The results also showed good content validity and internal consistency (Cronbach’s alpha: 0.86–0.93) [59].

The Autism Quotient-Child (AQ) is a 50-item parent-report questionnaire using a Likert scale to assess autistic traits in children aged 4–11 years [60]. Parents will be asked to rate the extent to which they agree or disagree with statements about their child, using the following answer categories: 0 representing definitely agree; 1 slightly agree; 2 slightly disagree; and 3 definitely disagree. The Likert response format helps parents assess their children’s difficulty level, which is useful for screening for ASD and determining the severity of symptoms. The scale includes reverse items (1, 3, 8, 10,11, 14). Overall, the score range is from 0–150, with higher scores (76 and above) suggesting the presence of ASD traits. The sum of each item score represents the total AQ score, where a minimum AQ score of 0 indicates no autistic traits, and a maximum score of 150 suggests full endorsement of all autistic traits. The AQ-Child has been translated into multiple languages, with the Malay AQ-Child version demonstrating good reliability and validity with a Cronbach’s alpha value of 0.82 [61].

Moreover, the Strength and Difficulties Questionnaire (SDQ) is a 25-item parent-rating screening tool used to screen a child’s behavioural and emotional problems [62]. SDQ comprises five subscales: conduct problems (e.g., fighting with others, well-behaved), hyperactivity (e.g., restlessness, easily distracted), emotional symptoms (e.g., frequent worries, often unhappy), peer problems (e.g., being picked on or bullied, liked by other children), and prosocial behaviour (e.g., being considerate of others, shares with other children) [62]. Each subscale contains five items. Each item is rated on a 3-point response scale: 0 = not true, 1 = somewhat true, and 2 = certainly true. The scores from each domain will be summed, and a ‘total difficulties score’ will be calculated by summing the four deficit-focused subscales (excluding prosocial behaviour). Z-scores will be calculated for each domain, with higher Z-scores indicating fewer difficulties. The cut-off scores for ‘borderline’ and ‘abnormal’ classifications correspond to the 80th and 90th percentiles (20th and 10th for prosocial behaviour scale), respectively. Specifically, scores falling within the bottom 10% of the normative distribution indicate potential problems of clinical significance. The Malay version of parent-rated SDQ is readily available and has shown acceptable internal consistency, with Cronbach’s alpha values above 0.70 for all subscales, except for conduct and peer problems [63].

Children’s sleep quantity and quality will be assessed using two tools: the BEARS Sleep Screening Tool [64] and the Children’s Sleep Habit Questionnaire (CSHQ) [65]. BEARS is a brief, clinician-administered screening tool designed to identify common sleep issues in toddlers, preschoolers, and school-aged children. It includes five items and incorporates five basic sleep domains: Bedtime problems, Excessive daytime sleepiness, Awakenings during the night; Regularity of sleep/wake cycles and average sleep duration; and Snoring. These domains reflect the most common presenting sleep complaints in children. The clinical use of BEARS has been correlated with improved detection/diagnosis of sleep problems in children aged 2–12 years [64]. Besides, to assess sleep disorder scores among children with ASD, the 33-item abbreviated version of CSHQ will be used [65]. CSHQ is a more detailed parent-reported questionnaire that assesses sleep quality through eight subscales, each measuring specific types of sleep problems that will be summed up to a total sleep disorder score that indicated an index of sleep quality. Each item will be rated on a 3-point Likert scale, with items 1, 2, 3, 10, 11, and 26 being reversely scored. The total CSHQ scores range from 33 to 99. A high total sleep disorder score indicated a high sleep disturbance.

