### Objectives

This study primarily aims to understand the role of oral and gut microbiota in the molecular mechanisms underlying the aetiology of ASD among children in Malaysia. Specifically, this study aims to determine whether there is an association between the oral and gut microbiota and socio-demographic factors, nutritional status, and autism severity among children with ASD compared to TD healthy children. Additionally, this study also measures additional independent variables to determine the associations between oral and gut microbiota and gastrointestinal symptoms, eating behaviour, behavioural profiles and sleep quality.

The hypothesized relationships between gut microbiota, nutritional status, dietary intake, and ASD severity are illustrated in Fig 1.

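### The only handling fixed for the 0–12 gastrointestinal score is a high/low split at 3; if that split is what is analysed, the microbiota–GI association in 28–40 boys with ASD loses power

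*Protocol article*

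**What the plan says.** All references are to the protocol article.

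- *Parent report questionnaires* describes the modified index, "which encompasses six items: constipation, diarrhoea, stool consistency, stool smell, flatulence, and abdominal pain". Parents rate each item "with scores of 0, 1 or 2 based on the severity and frequency of the symptoms experienced over the past three months".
- The same section then classes the total: "A total score of 3 or higher will be considered a high score, while a score of below 3 will be considered as a low" one. It gives no other rule for handling the total.
- It also reports reliability, for the total: "The total GI score has a high intraclass correlation of 0.95".
- *Objectives* lists, as an additional aim, "to determine the associations between oral and gut microbiota and gastrointestinal symptoms, eating behaviour, behavioural profiles and sleep quality", and calls these measures additional independent variables. The abstract likewise puts gastrointestinal symptoms among the independent variables; the dependent variables are the microbiota profile and autism severity.
- *Statistical analysis plan* names GI symptoms once, in the sentence on associations within the ASD group: "gastrointestinal symptoms, and nutritional status among children with ASD will be modelled using mixed-effects logistic regression (MELR) model and random forest". It does not say whether the score enters as the total or as high/low.
- *Sample size* sets recruitment at 40 boys with ASD and allows for 30% dropout.

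**The concern.** The split puts a boy with a total of 3 (for example, three items at level 1) in the same class as a boy with 12, and separates totals of 2 and 3 as if they differed in kind. Any gradient in the microbiota across GI severity within either class is lost.

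The microbiota–GI association is a stated aim and is modelled only within the ASD group, so 28 to 40 children carry it. A sample of that size has little information to spare. An analyst who follows the article as written finds one instruction for the total, and that instruction is the split.

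**Working it through.** **What the document gives.**

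- Range of the total: 6 items × 0–2 = 0 to 12.
- Cut: 3 or more is high.
- Number of boys with ASD: 40 recruited; 40 × (1 − 0.30) = 28 if the stated dropout occurs.
- No power, alpha, effect size or expected share of high scorers is stated for this association, so there is no plan figure to reproduce.

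**What has to be assumed.** The correlation r between the GI score and a microbial measure (such as a diversity index), two-sided alpha of 0.05, and the proportion p of boys scoring high.

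**Formulas.**

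- Power for a correlation by Fisher's z: m = atanh(r) × √(n − 3); power = 1 − Φ(1.96 − m) + Φ(−1.96 − m).
- Cutting a normally distributed score so that a proportion p is high multiplies r by φ(z_p)/√(p(1 − p)), where z_p is the normal quantile at p. The factor is 0.399/0.5 = 0.798 at p = 50%, 0.759 at 30% and 0.700 at 20%.

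**Worked case, n = 40, r = 0.4, p = 50%.**

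- Uncut: m = 0.4236 × √37 = 2.577, so power = Φ(0.617) = 73.1%.
- Cut: r becomes 0.4 × 0.798 = 0.319; m = 0.3307 × √37 = 2.012, so power = Φ(0.052) = 52.1%.
- Loss: 21.1 points (from unrounded values).

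**Power with the total, power with the split, and points lost, at an even split.**

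| r | n = 28 | n = 40 |
|---|---|---|
| 0.1 | 7.9% vs 6.9% (1.1) | 9.4% vs 7.8% (1.6) |
| 0.2 | 17.3% vs 12.7% (4.7) | 23.4% vs 16.5% (6.9) |
| 0.3 | 34.0% vs 23.1% (11.0) | 46.9% vs 31.8% (15.2) |
| 0.4 | 56.3% vs 38.0% (18.3) | 73.1% vs 52.1% (21.1) |
| 0.5 | 78.4% vs 56.0% (22.4) | 91.6% vs 72.9% (18.8) |
| 0.6 | 93.4% vs 74.1% (19.3) | 98.8% vs 88.7% (10.1) |
| 0.7 | 99.1% vs 88.4% (10.8) | 100.0% vs 97.0% (3.0) |

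Over r = 0.3 to 0.6 the loss is 10.1 to 22.4 points.

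**Sensitivity.**

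- Uneven split, r = 0.3 to 0.6: 13 to 27 points lost if 30% score high; 15 to 34 if 20% do.
- Stricter alpha of 0.001 with r = 0.4 and an even split: 7 points lost at n = 28 and 14 at n = 40.
- Simulation of six 0–2 items, summed and cut at 3 (Pearson test on the total versus t-test on the split; correlation with latent severity 0.4 to 0.6): losses of about 10 to 21 points when 23% to 64% scored high, and 12 to 29 when about 11% did. The mean observed correlation with the total was 0.28 to 0.49 in the first group of settings. This check does not rely on a normally distributed total.

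**The case against.** The strongest objection is that the article fixes a label and not an analysis variable. The cut stands in the description of an instrument. Neighbouring instruments also have labels (76 and above on the AQ, borderline and abnormal bands on the SDQ, the growth z-score classes), and a label need not mean that the score behind it is discarded. The reliability quoted for the total suggests that the total is itself of interest, and the functional form of one secondary predictor is often left to a fuller plan. Much of this stands: nothing in the document says that the total is dropped. What remains is that the split is the only handling of this total that the article fixes, whereas the CEBQ, for example, is given an explicit numeric scoring as subscale means.

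A reader might infer more than the document supports:

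- **That the logistic model implies the cut.** It would do so only if GI symptoms were the outcome. The abstract and *Objectives* make them an independent variable, and both logistic regression and random forest accept a 0–12 predictor.
- **That the split leaves residual confounding by GI severity.** The confounders named are age and socioeconomic status; GI severity is not listed as an adjustment variable.
- **That the cut is unsound because it comes from an earlier publication.** It is cited and set in advance, and its origin does not show it to be invalid.

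It is also fair to object that the power figures are for simpler tests than those planned, at an unadjusted 5%, although *Sample size* applies a false discovery rate to secondary microbiota comparisons. That limits how precisely the loss can be stated.

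**Conclusion.** The point holds in conditional form. The article fixes a high/low split of a 0–12 score, and its analysis section does not restore the total. If the split is analysed, the approximate loss of power at two-sided 5% with an even split is 10 to 22 points for correlations of 0.3 to 0.6, 1 to 7 points at 0.2 or below, and 3 points at 0.7 with 40 boys. It is larger if few boys score high.

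Only the sample sizes come from the document; correlation, alpha and split are assumed. The figures indicate the order of the loss and are not an estimate for the mixed-effects model. Every setting computed showed a loss. An unconditional statement that the plan costs this association a set amount of power would go beyond the text. At the weakest correlations neither form has useful power (below 24% at r = 0.2), so the choice matters mainly for moderate associations. The change is worth making because it is nearly free.

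**What to change.** In *Parent report questionnaires* and *Statistical analysis plan*, state that the 6-GSI total (0–12) enters the association models as a numeric or ordinal independent variable, in keeping with its role in the abstract and *Objectives*. Say that the high/low split at 3 is for description only.

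The cost is wording: the six items are already collected. The one drawback is that results become associations per point of the score, which compare less directly with publications that use the cut; a descriptive table by high/low class would keep some of that comparability. Data collection is expected to run to June 2026, so the form of the variable can be settled before analysis.
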